
**Follow up procedures**

We anticipate locating and re-enrolling a sizable proportion of the PROMISE-EBF cohort in

Burkina Faso and Uganda. Though the scheduled follow-up of children in the EBF-trial was up to

6 months, follow-up studies have been carried out and published from Burkina Faso at 12 months of age and in Uganda at 2 years of age. These follow up studies had very good overall follow up rates of over 70%, just like the original study (figure 4). A recently concluded study followed up the Ugandan cohort between age 3 and 4 years. The very high follow-up rates were achieved because of the involvement of members in the local communities during data collection. We used recruiters from the clusters to identify the pregnant women. The same recruiters were involved in the 12 and 18 months as well as the 3-4 year follow-up studies in Burkina Faso and Uganda. We also have access to Global Positioning System (GPS) data for the homesteads. Based on previous follow-up data from the PROMISE-EBF study and its subsequent cohort studies, our teams in Centre MURAZ (Burkina Faso) and in Mbale District (Uganda) have different source data and qualified personnel to retrieve a high proportion of children initially enrolled, for their re- inclusion in the PROMISE-SB study. The following useful information and source data are locally available in each of the sites:

1) Full names and dates of birth of all children included in the PROMISE-EBF trial and its subsequent cohort studies per village.

2) Full names of the parents of each child (including nick names when relevant)

3) List of the GPS-coordinates of the households involved in the PROMISE-EBF trial.

4) Members of staff from the PROMISE-EBF study are still in place and can be re- contracted to take part in the PROMISE-SB study and they will be an asset for our teams in retrieving the PROMISE-EBF children. Key personnel who are still available include study coordinators, recruiters, peer-counsellors and data collectors.

We estimate that within a period of 3 months our teams will be able to retrieve over 70% of children initially enrolled and who are still alive. We will request for re-consent for inclusion in the PROMISE-SB study. Data collection is expected to last 12 months.

Figure 4: Follow up in the original study (A=Burkina Faso, B=Uganda)

[figure not shown]

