**3.0 STUDY PROCEDURES**

**Overview**

This study will examine the association between promotion of peer counselling for EBF in the

first 6 months of life and human capital including: 1) cognitive function; 2) behavioural and emotional status; 3) educational readiness and attainment; 4) health status; 5) fine and gross motor skills; 6) physical growth and body composition; and 7) changes in household economic status. Below we present items 1, 2, 3 under **mental health;** 4, 5 and 6 under **somatic health** and lastly 7 under **productivity**. We will also assess moderators and confounding factors.

The PROMISE-EBF trial was a community-based, cluster-randomized trial promoting peer counselling for exclusive breastfeeding (EBF) in the intervention group. Peer counsellors living in the intervention clusters were identified and trained for one week. The course material was based on the WHO courses: Breastfeeding counselling: a training course, and HIV and infant feeding counselling: a training course [19, 20]. The courses were integrated and adapted to local circumstances. The counsellors offered home-based breastfeeding peer support to the mothers in the intervention clusters. Peer counsellors received continuous supervision (fortnightly to monthly) by study-appointed supervisors. At least five home visits were scheduled for all women in the study starting with a visit in the third trimester of pregnancy. Peer counsellors provided information, and encouraged and supported EBF for 6 months. Mothers with any breastfeeding difficulties were referred to a health worker with training in lactation management. The control group received the standard of care within the respective countries [1].

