|  | **Activity 1.4 :**  Enroll participants | **Minimum of 428 (404 + 6% attrition) of original EBF intervention and control groups enrolled in Uganda traced and enrolled;**  **selection biases are identified and randomization integrity confirmed.**  **Minimum of 428 (404 + 6% attrition) of original EBF intervention and control groups in Burkina Faso traced and enrolled;**  **selection biases are identified and randomization integrity**  **confirmed.**  Indicator of success: 70% (604+626) of original EBF intervention and control groups enrolled in each site. | Loss to follow up | Use GPS coordinates and other information to trace participants | October  2012-March  2013 |
| --- | --- | --- | --- | --- | --- |
| **Activity 1.5:** Assess health, nutrition and socioeconomic (SE) status | Community level confounders captured and assessed.  Data collection complete | Recall and information bias  Technical faults with software and computers | Use of community based data collectors  Data backups  Use available records  Technical support staff | March 2013- May 2014 |
| **Activity 1.6**  Assessment of  neurodevelopment, cognition, behavior / | **Assessments completed on**  **94% of enrolled participants tracked to date in Uganda**  **(June 2013).** | Information bias | Blinding of data collectors as to which group received peer counseling* | April 2013- May 2014 |

[figure not shown]

|  | emotion and school readiness | **Assessments completed on**  **94% of enrolled participants tracked to date in Burkina Faso (June 2013).**  Assessments complete on minimum of 404 of original EBF intervention and control groups in each site (Uganda and Burkina Faso) with comparability of scores validated on a random 10% of double-scored assessments from two assessors.  Indicator of success: 70% (604 in Uganda, 626 in Burkina Faso) of original EBF intervention and control  groups enrolled in each site. |  |  |  |
| --- | --- | --- | --- | --- | --- |
| **Activity 1.7**  Neuroimaging of a  subset of Ugandan participants | MRI analysis is conducted according to the inclusion plan. | Guardians or parents of children with neurocognitive abnormalities might refuse neuroimaging  MRI machine could break down  Loss of MRI data | Give detailed information about the study especially the need and safety of MRI. Separate consent for MRI  Arrange for alternative MRI (Kololo and Mulago Hospitals)  Back up copy of images | April 2013- May 2014 |

[figure not shown]

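### The protocol allows peer counsellors, who worked only in intervention clusters, to help retrieve children, so re-enrolment may differ by arm

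*Protocol*

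**What the plan says.** Section 3.0, Follow up procedures, item 4, states that former staff of the original trial are still in place and can be re-contracted, and that "they will be an asset for our teams in retrieving the PROMISE-EBF children". It then names the cadres: "Key personnel who are still available include study coordinators, recruiters, peer-counsellors and data collectors".

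The Overview of section 3.0 says where the counsellors worked: "Peer counsellors living in the intervention clusters were identified and trained for one week". They gave home support to mothers in those clusters. For the other arm it says only: "The control group received the standard of care within the respective countries". One sentence there speaks of home visits scheduled for all women in the study. The sentences around it, and the Executive Summary, place the visits in the intervention arm.

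The other tracing resources are not tied to an arm. Item 4 follows lists of children's and parents' names and of household GPS coordinates. On recruiters the section says "We used recruiters from the clusters to identify the pregnant women" and "The same recruiters were involved in the 12 and 18 months as well as the 3-4 year follow-up studies". In Appendix I, Activity 1.4, the mitigation for loss to follow-up is "Use GPS coordinates and other information to trace participants".

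The same activity sets the enrolment targets for each country over both arms together, with the milestone that "selection biases are identified and randomization integrity confirmed". It gives no criterion by arm.

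**The concern.** Randomisation protects a comparison made years later only as far as being found again does not depend on arm. The protocol credits its good earlier follow-up to the involvement of local community members. Peer counsellors are such people: at least five contacts with each mother were scheduled, from late pregnancy, but in one arm only. If familiar local staff raise retrieval, this cadre raises it in intervention clusters and not in control clusters.

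The planned loss is large enough for this to matter, at up to 30% under the success indicator and about half under the minimum. If the extra families found in one arm differ in outcome from those found by the common tools, the arm difference is biased. The planned adjustment for baseline differences deals only with what was measured.

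There is a second, related effect. In the original trial, data collectors were kept apart from peer counsellors to limit information bias (Sites and sampling procedures). Appendix I, Activity 1.6, relies on blinding data collectors to which group was counselled. Item 4 puts both cadres in one pool for retrieval and does not restate the separation. A counsellor who helps trace a family may reveal the cluster's arm before parent-reported outcomes such as the SDQ are collected.

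**Working it through.** **1. The plan's own figures.** Enrolment was 863 women in Uganda and 895 in Burkina Faso (Sites and sampling procedures).

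- 70% target: 0.70 × 863 = 604.1 and 0.70 × 895 = 626.5. The stated 604 and 626 reproduce.
- Minimum: 404 × 1.06 = 428.2. The stated 428 reproduces.
- The minimum as a share of those enrolled: 428/863 = 49.6% and 428/895 = 47.8%.

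**2. Can the pooled targets be met with unequal arms?** The protocol gives no enrolment by arm, so assume an even split in Uganda, 431.5 per arm. Retrieval of 80% and 60% gives 345.2 + 258.9 = 604.1. The success indicator is met despite a 20-point gap between arms.

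**3. Illustrative bias.** The protocol gives neither retrieval by arm nor the outcome gap between easy- and hard-to-trace children. Both are assumed here, and so is an SD of 15 for conversion to points. There are two ways to define the gap.

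(a) D is the gap between retrieved and unretrieved children, equal in both arms, with the unretrieved scoring lower. In an arm with retrieval p, the retrieved mean exceeds the full-arm mean by (1 − p) × D. The bias in intervention minus control is [(1 − p_int) − (1 − p_ctrl)] × D = −(p_int − p_ctrl) × D.

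(b) D is the amount by which the extra families, found only because of the added resource, score below the other retrieved families. The bias is −[(p_int − p_ctrl)/p_int] × D.

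| Definition | Retrieval, intervention v control | Bias at D = 0.1 SD | Bias at D = 0.5 SD |
|---|---|---|---|
| (a) | 70% v 70% | 0 | 0 |
| (a) | 75% v 65% | −0.010 SD (0.15 points) | −0.050 SD (0.75 points) |
| (a) | 80% v 60% | −0.020 SD (0.3 points) | −0.100 SD (1.5 points) |
| (b) | 80% v 70% | −0.0125 SD (0.2 points) | −0.0625 SD (0.9 points) |
| (b) | 80% v 60% | −0.025 SD (0.4 points) | −0.125 SD (1.9 points) |

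The size therefore runs from about 0.01 to 0.13 SD. The minus sign means that better tracing in the intervention arm pulls the estimate against the intervention. If harder-to-trace children score higher, the sign reverses.

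**The case against.** The strongest reply is that item 4 is an inventory of what is available, not a procedure. It says that staff can be re-contracted, and nothing in the protocol assigns counsellors a tracing task. The Implementation section and the Staffing plan give consent and parent interviews to data collectors. The Approach paragraph of the Executive Summary names recruiters and GPS data for tracing, not counsellors. Names, GPS lists and recruiters serve both arms. With about 36 to 37 enrolled women per cluster (863/24 and 895/24), one more tracer may add little, and gaps of 10 to 20 points may be too large. Data collectors also return to the clusters that they covered before, so some may already know the arm.

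Much of this stands. A reader might infer that the protocol makes tracing arm-dependent and so builds selection bias into re-enrolment. The text does not support that: it permits such tracing without prescribing it, and bias also needs retrieval that in fact differs by arm and is related to outcome. Nor does the text support counsellors obtaining consent or collecting outcomes.

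Three parts of the reply do not clear the point. The Staffing plan does not settle the matter, because it also omits recruiters, on whom the earlier follow-up relied. Tools shared by both arms do not cancel an extra one in a single arm. And the milestone on selection bias comes after the event: finding an imbalance does not undo it.

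**Conclusion.** The point holds as a moderate weakness. The protocol names an intervention-only cadre as useful for retrieval, gives control clusters no equivalent, does not bar that cadre from tracing, and sets retrieval targets that cannot show a difference between arms. It permits differential re-enrolment but does not make it certain.

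The range of 0.01 to 0.13 SD rests wholly on assumed retrieval gaps (10 to 20 points) and outcome gaps (0.1 to 0.5 SD). It shows what could happen and does not predict it. If harder-to-trace children score lower, the effect would be to hide a benefit, not to create one.

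A reader might also infer that the upper end equals the effect the trial could expect, by multiplying the 5-point IQ difference in the literature review by the 40-point contrast in exclusive breastfeeding. The documents do not support this. The 5 points compare breastfed with non-breastfed children, whereas the same review says that most children in both arms here are breastfed and that the arms differ in exclusivity.

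The risk to blinding is real but secondary, for the same reason: it arises only if counsellors are used.

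**What to change.** - In Follow up procedures, item 4, remove peer counsellors from the personnel listed for retrieval. State that they take no part in tracing, consent or data collection.
- State that both arms are traced by the same cadre (recruiters, with the name and GPS lists) and with the same number of contact attempts.
- In Appendix I, Activity 1.4, check the retrieval milestone by arm as well as pooled.

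These are changes of wording and staffing. The likely cost is slightly lower retrieval in intervention clusters. They need to be in place before tracing starts, because differential retrieval cannot be reversed afterwards.

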**Assessments**

The assessments will be done through three steps: 1) a home-session which will involve obtaining

an informed consent and parent interviews using structured questionnaires, 2) a clinical and psychometric assessment session of the child, and 3) teacher structured interviews when applicable. The home sessions and clinical sessions will be on different days with the home session coming first.

A home-session will involve assessment of the household status including confirmation that the child is still alive. In the event of a child death, an appointment will be sought for a verbal autopsy.

For live children with informed consent, the home-session, estimated to last about 1-2 hours will include the following: 1) Updates of the socio-demographic information of the household including food security, 2) morbidity (history and current status) of the child, 3) history of intentional and unintentional injuries of the child and caretaker, 4) productivity including schooling and work related activities of the household members, 4) moderators/confounders and

5) parental structured interviews on own and child’s mental health and related factors

The assessment of each child will be done in a group setting, avoiding a single child and single investigator interaction which would be perceived as in an unfamiliar and strange environmental situation. We aim to mimic a ‘school’ situation but, importantly, the children will be scored individually. This group setting is believed to be more child and family friendly, because studies in low-income countries have shown that children in these areas perform better when in the company of other children [21]. A play area within the test sites will be set up for this purpose.

A clinical child assessment will include the following, estimated to take approximately 2-3 hours: medical and developmental history, physical and neurological exam, fine and gross motor skills assessment, anthropometry measures, audiology and visual acuity testing, cognitive testing, laboratory tests: including minimum haemoglobin, CRP and malaria screening. The children and their mothers/guardians will be allowed breaks in between the assessments, and the study team will provide a meal before start-up of the assessment. Any identified illnesses will be referred to the appropriate local or regional health service. When possible, appropriate services will be provided in collaboration with the local health system and NGOs during the period of data collection, for example ophthalmologist and glasses for visual problems, malaria treatment or referral for HIV testing.

**Somatic health**

*Mortality*

The PROMISE-EBF trial has collected and published data on perinatal, neonatal and infant mortality in Burkina Faso and Uganda. For this study, we will collect data on child deaths after infancy. Information on all deaths will be collected and classified using a standard World Health Organization (WHO) verbal autopsy questionnaire that has been validated in both countries and used by our team [8].

*Morbidity*

Using standardized questionnaires, the original PROMISE-EBF trial and subsequent follow-up studies have collected data on immunization, hospitalizations, acute infections (malaria, diarrhea, cough and fever), intentional and unintentional injuries. We will conduct repeated data collection on these topics as the children now are older.

**Clinical examination**

*Clinical and neurological assessment*

A doctor with assistant nurses will review the medical history including the *10 Questions plus* [22] and conduct a physical and neurological exam. Heart rate, blood pressure and body temperature measurements will be recorded. The diagnostic screening of motor disabilities will be assessed according to a structured neurological assessment covering: mental status, cranial nerves, reflexes, motor system: tone; strength/power; gait; coordination and sensation. Diagnosis of cerebral palsy, post-polio paralysis, limb abnormalities and other severe medical conditions will be made on the basis of the medical and neurological assessments. The study will refer children with medical conditions to the health facilities.

*Anthropometry*

Weight will be measured using standardized Seca® digital scales to the nearest 0.1kg. We will use a Seca stadiometer® in the 263 series, to measure height. Anthropometric indices will be calculated assessing weight-for-height, height-for-age, weight-for-age and body mass index (BMI)-for-age z-scores. To measure body composition, mid-upper arm circumference (MUAC), triceps skinfold and subscapular skinfold will be measured. Head circumference will also be measured. For the above measurements z-scores will be calculated using WHO Child Growth Reference 2007 [(www.who.int/childgrowth/en](http://www.who.int/childgrowth/en)). Standardization to minimize technical error of measurement (TEM) will include regular refresher training, assessing precision and reliability of data collectors.

*Fine and gross motor skills*

We will use *The movement assessment battery for children* (Movement ABC or M ABC) consisting of 8 items addressing manual and ball skills and balance (table 4) [23]. Total standard scores and age-specific norms and standard deviations will be presented.

able 4: Test items form age band 3 of the Movement ABC

[figure not shown]

*Visual acuity*

Visual acuity will be assessed using the “Illiterate E chart” (Snellen E chart). This chart does not depend on literacy or familiarity with an alphabet. It is therefore effective in assessing children with cognitive and developmental disabilities who may have higher rates of visual problems than others [24,25]. The diagnostic assessment of vision impairment and eye disease will be made by qualified personnel and the diagnostic criteria will be in accordance with World Health Organization criteria on vision impairments.

*Auditory*

A clinician will assess hearing using otoacoustic emissions (OAEs), tympanometry and conventional and/or conditioned play audiometry (CPA) adapted from Berg and colleagues [26]. To assess middle ear status, we will use low-frequency (220 or 226 Hz) tympanometry. We will determine the type and degree of hearing impairment based on the WHO criteria, 2002. The study team will be trained in the use of OAEs, tympanometer, and audiometer before the study begins.

*Nutritional status*

Having been a nutritional intervention, we have an extensive database of feeding data. Using food frequency questionnaires, data on feeding history was collected at 3, 6, 12 and 24 weeks of age. Data on complementary feeding was also collected at 18 months and 3-4 years of age in Uganda and at 1 year of age in Burkina-Faso. For this study, we shall collect data on food frequency in the past 7 days using food frequency questionnaires that we have already used in our population. Data on food security will be collected based on the food and agricultural organization standards. As mentioned earlier, haemoglobin levels will also be measured.

*Laboratory assessment*

Finger prick screening will be done to assess haemoglobin status, C-reactive protein and malaria parasitaemia. Children with abnormal laboratory findings indicating illness or deficiency results will be referred for further investigation. After careful consideration, we have decided not to include HIV-testing, but only refer for counseling and testing where clinical suspicion warrants it. The reasons are that 1) few children are likely to be infected (in Uganda the HIV-prevalence is

0.7% among children (maximum 4-5 children in our cohort) and in Burkina the prevalence among adults is around 1% and therefore much less in children; 2) infected children born 5-7 years ago are likely to be either deceased or symptomatic; 3) any undiagnosed, asymptomatic HIV- infections is unlikely to measurably bias the exposure-outcome association of interest because of the low prevalence (1); and 4) having an HIV-test in the study commits a lot of resources with risk of deferring families and children from the study.

**Mental health**

*Cognition and memory*

The team will use the Kaufman Assessment Battery for Children (K-ABC), the Luria-version which is to a large extent overlapping, but less language-dependent than the newer version KABC-II from 2004. Kaufman Assessment Battery for Children (K-ABC) was used and reliability checked for these contexts [27]. As a supplement Raven Progressive Matrices as a measure of intellectual function will be used. This has also been extensively used in Africa [28].

*Behavioural and emotional factors*

This study will apply the relatively short Strengths & Difficulties Questionnaire (SDQ) ([http://www.sdqinfo.com/)](http://www.sdqinfo.com/) for a gross assessment of behavioural and emotional factors. This is a screening tool with 25 items on 5 scales. When indicated, the child will be referred for further assessment to appropriate authorities. When applicable, we will administer the SDQ for teachers.

*Mental health co-morbidity assessment*

If any of the SDQ-scorings or home structured interviews and the assessment of the child give an indication for serious mental health challenges for the child, the study team will refer the child for follow-up investigation for potential diagnosis of: inattention and impulsiveness, autism-spectrum disorders, anxiety, depression, compulsive disorders, Tourette/tics, trauma and attachment difficulties. Counseling, therapy and treatment will be covered by the study team when feasible. Consent for information on diagnostic conclusions will be sought for.

